### Step 2: Development of change objective matrices

#### Program objective and outcomes

The needs assessment resulted in set of three key behaviors, physical activity, diet and regulation challenges, which were translated into ten program objectives (Table 1): 1) increase daily physical activity levels, 2) decrease sedentary time and screen viewing time, 3) establishing regular meal patterns, 4) increasing number of family meals, 5) regulate/decrease portion sizes, 6) increase intake of healthy food and beverages and decrease intake of unhealthy alternatives, 7) establish adequate sleep duration patterns, 8) increase self-esteem, 9) strengthen autonomy support (parents), and 10) strengthen autonomous regulation and self-efficacy (parents). In addition, two subsidiary program objectives were described: 1) reducing BMI-for age S-score (iso-BMI) and 2) improve self-perceived health.

**Table 1 Tab1:** Specific program objectives of the intervention study

Key behaviors	Main objectives
ᅟPhysical activity	1. Increase daily physical activity levels
	2. Decrease sedentary time and screen viewing time
ᅟDiet	3. Establish regular meal patterns
	4. Increase number of family meals
	5. Regulate/decrease portion sizes
	6. Increase intake of healthy food and beverages and decrease intake of unhealthy alternatives
	*Sub-goals:* Lower the energy density of frequently consumed food and beverages: • Incorporate a large portion of fruits and vegetables into meals • Lean meats • Whole grains, legumes • Low-fat dairy products • Water instead of sugary beverages to quench thirst • Consume appetizers low in energy density
ᅟFamily structure	7. Establishing adequate sleep duration patterns
	8. Increase self-esteem
	9. Strengthening perceived autonomy support (parents)
	10. Strengthening autonomous regulation and self-efficacy (parents)
Health indicators	Subsidiary objectives
ᅟBMI/perceived health	1. Reduced BMI-for-age z-score (Iso-BMI)
	2. Improved self-perceived health

Performance objectives specify the behavioral action that the target groups have to perform in order to successfully change behavior. Because changes in lifestyle habits as part of a weight-management requires long-term self-management skills to regulate and adapt behavior to changing circumstances, self-regulation models were used to guide the creation of the performance objectives. An example of performance objectives is illustrated in Table 2.

**Table 2 Tab2:** Performance objectives for improving healthy dietary habits and a meal patterns- an example

Self-regulation phase	Performance objectives
Monitoring phase	1. Families monitor current dietary habits and reflect on their own habits
Motivation phase	2. Families decide to participate in the program
	3. Families decide to challenge themselves and be actively involved in group sessions
Goal setting phase	4. Families set maximum three challenging but attainable goals to improve dietary habits
Active goal pursuit	5. Parents plan meal for weekdays including purchase of food and beverages according to plan
	6. Families have a regular meal pattern and decide to have one family meal every day
	7. Parents serve adequate portion size to their child
	8. Families select and try healthy alternatives to unhealthy food and beverages
	9. Families understand and resist temptation to increase intake of unhealthy food and beverages
	10. Parents buy and serve food healthy food and beverages regularly and reduce the availability of unhealthy alternatives
Evaluation phase	11. Families evaluate their achievements according to goals
	12. Families make long-term planning to maintain their newly acquired behavior

Further, important and changeable determinants for healthy lifestyle behaviors were selected. The personal determinants selected for increased physical activity and reduced sedentary time were 1) knowledge, 2) awareness, 3) attitude, 4) skills, 5) self-efficacy and 6) intention. In addition, social influence and availability (related to equipment and local facilities) were identified as important environmental determinants for physical activity and sedentary behavior.

The personal determinants selected for improving dietary habits were 1) knowledge, 2) awareness, 3) attitude, 4) skills and 5) self-efficacy. Social influence and availability of different food items and beverages were identified as important environmental determinants for dietary habits.

Change objectives were created by crossing the performance objectives with the selected determinants in matrices. An example of change objectives is illustrated in Table 3.

**Table 3 Tab3:** Performance objectives related to changes in determinants with regard to improve dietary pattern- an example

	Personal					Home environment	
	Knowledge and risk-perception	Awareness	Attitude	Skills (self-regulation)	Self-efficacy	Social influence /reinforcement	Availability
Families select and try healthy alternatives to unhealthy food and beverages	1. Families are able to distinguish between healthy and unhealthy food and beverages 2. Families can describe the problems associated with increased intake of unhealthy snacks and drinks 3. Families can identify healthy alternatives to unhealthy snacks and drinks	1. Families can describe the health benefits of a high intake of healthy food and beverages (especially focus on increased intake of vegetables)	1. Families feel positive about making changes to increase intake of healthy food and beverages 2. Families express a positive attitude toward choosing healthy alternatives to unhealthy snacks and drinks	1. Families can explain to others the problems associated with a high intake of unhealthy food and beverages 2. Parents demonstrate setting appropriate limits for children regarding intake of unhealthy food and beverages 3. Families practices skills to ask for healthy alternatives in different settings 4. Families taste healthy alternatives to unhealthy snacks and drinks	1. Families express confidence in ability to recognize healthy and unhealthy food and beverages 2. Families show confidence to select healthy snacks and drinks 3. Families show confidence to try new snacks and drinks	1. Parents praises child for increasing healthy eating habits 2. Parents and other family members decrease intake of unhealthy food and beverages	1. Parents increases the availability and accessibility of healthy snacks and drinks at home 2. Parents reduces the availability and accessibility of unhealthy snacks and drinks at home

### Step 3: Selection of theory-based methods and strategies

#### Theoretical framework of the present study

To improve our understanding of how interventions effect change, we need to use precise and scientific methods for linking behavioral change theory to designing and evaluating interventions. Intervention descriptions are often not specific about the techniques employed and there is no clear correspondence between theoretical framework and adoption of particular change techniques [50, 51].

During the third step of the IM protocol, theory-based methods that were capable of changing the determinants were identified and chosen. An ecological approach was used when developing the intervention, which support the use of a multiple theories, as opposed to one single theory [31]. The present research program, however, used Self-Determination Theory (SDT) [52] as the main theoretical framework. Health-related behaviors are more likely to be initiated and maintained when the patients experience self-determination. This is done by maximizing the participants’ experience of the basic psychological needs of *autonomy*, *competence,* and *relatedness* in health care settings [53]. According to Basic Need Theory [54], a mini-theory within the Self-Determination Framework, the three innate needs must be satisfied for individuals to achieve positive development and optimal motivational function [53, 54]. The more autonomously regulated an individual is towards a given behavior, the greater effort, engagement, persistence, and stability the individual is likely to produce [55], and autonomous regulation has been identified as one of the key predictors of successful behavioral change [56]. The Norwegian Directory of Health [32] recommends MI as a counseling technique for the HLC’s. SDT may represent a theoretical approach to understand how MI works, and the two approaches may to some extent be integrated [57]. Meta-analysis of randomized controlled trials supports the effectiveness of MI in behavioral change and weight-loss treatment among adults [58]. MI supports the participants’ need for autonomy, relatedness and competence by allowing the participants freedom to explore reasons for and against change (autonomy) in a non-judgmental context (relatedness) and evoking changes that are realistic and attainable (competence) [55].

In addition to SDT, tools and materials used in the present study are also based on several other theoretical models, including the Health Believe Model, the Trans-Theoretical Model, the Precaution-Adoption Process Model, Persuation-Communication Matrix, Social Cognitive Theory, theory of Self-Regulation, Goal Setting Theory, Theory of Planned Behavior and Theories of Learning. The link between theoretical models, practical strategies, materials and tools are described in detail in Table 4.

**Table 4 Tab4:** Description of methods and strategies used in the intervention study

Determinant	Theoretical methods	Strategy	Tools/materials
*1) Personal*			
Knowledge and risk perception (Diet, PA, Screen-time)	Consciousness raising (HBM; TTM)	Providing written and verbal information about the study	Letters sent to all parents of children in preschool and 3^rd^ grade providing information about the research study and target group Public health nurse (PHN) contact the target group (parents) by phone and invite them to participate in the study. An information folder, which explains participatory process to parents, is sent to their home-address or delivered during their first consult
		Provide tailored information to increase healthy lifestyle habits during the intervention period	Tailored brochures and information folders focusing on physical activity, diet, sleep and family structure
Awareness, risk perception & health believes (Diet, PA, Screen-time)	Information about personal risk (PAPM) Consciousness raising (HBM)	Personalized risk feedback from health screening	Expert registration/ monitoring and evaluation of BMI, dietary habits, physical activity level, sleep habits etc. in relation to national recommendations or recommendations by the research group
	Scenario-based risk information (PAPM)	Providing risk information	Tailored brochures focusing on long-term effects and information on benefits of healthy behavior
Attitude (Diet, PA, Screen-time)	Arguments (PCM) and feedback	Providing personal feedback to parents and children	PHN provides feedback on (perceived) positive consequences of healthy lifestyle habits Instructors give positive feedback during activity sessions
	Modeling (SCT)	Role models describing the benefits associated with a healthy lifestyle	Web movies
	Active learning (TSR)	Game promoting increased intake of fruit and vegetables	Rainbow shaped and colored vinyl sheets and colorful fruit and vegetable shaped self-adhesive stickers
Skills /self-regulation (PA) (Diet, PA, Screen-time)	Guided practice, active learning (SCT; TSR)	Organized activities with high intensity and different levels of coordination.	Tailored brochures and information folders describing how to organize different activities (for activity leaders) Information folders suggesting a variety of different high intensity exercises (for activity leaders)
		Provide specific suggestions for locally adapted parent-child leisure time activities (with high intensity) and strategies to reduce sedentary time/ screen time	Tailored brochures and oral information provided during individual family counselling meetings
		Parents and children prepare healthy meals together to improve hands-on practical cooking skills	A trained course coordinator. Detailed instructions describing necessary preparations and tips for conducting nutrition courses. Recipes for healthy dishes for all main meals
Self-efficacy (Diet, PA, Screen-time)	Goal setting and feedback (GST)	Formulation of maximum 3 challenging and feasible goals in close cooperation between health personnel and parents	PHN assist in goal setting using a contract that is signed by the parents
	Persuasive persuasion (SCT)	Encourage and convince parents to follow up the program	PHN-parents during individual family counselling meetings and power point presentations delivered as part of the course
	Guided practice, mastery experience, and feedback (SCT; TSR)	Organized activity groups (children) and cooking lessons (children and parents). Provide positive feedback whenever necessary and possible. Offer guided practice	Professional/trained instructors provide feedback during individual family counselling meetings and organized activity groups and cooking lessons
Intention (Diet, PA, Screen-time)	Autonomy building (SDT)	Motivational interviewing during individual coaching sessions	Trained PHN
	Persuasive communication (SCT)	Participation in group sessions, nutrition courses	Tailored educational material including power point presentations, verbal communication and information brochures
*2) Home environment*			
Social influence (Diet, PA, Screen-time)	Mobilize social support and resistance to social pressure (TPB)	Involve both parents, and significant others such as grandparents etc.	Tailored brochures and information folders and oral information provided during individual family counselling meetings
	Positive reinforcement (SCT)	Providing feedback evaluation of change process	The results from follow-up tests are delivered by PHN
Availability (Diet, PA)	Feedback, personal improvement, planning (TL; GST)	Practice in training, feedback on performance, and support with questions	Information folders and oral information provided during individual family counselling meetings and courses

*HBM* health believe model, *TTM* trans-theoretical model, *PAPM* precaution-adoption process model, *PCM* persuation-communication matrix, *SCT* social cognitive theory, *TSR* theory of self-regulation, *GST* goal setting theory, *SDT* self-determination theory, *TPB* theory of planned behavior, *TL* theories of learning

#### Strategies

The behavioral models and educational strategies are described in Table 4 and include individual family counselling meetings, nutritional courses, and physical activity groups providing general information, tailored information and practical learning sessions. Parents was at the same time encouraged to attend workshops intending to increase knowledge and awareness of regulation challenges, healthy eating habits and practical suggestions for implementing healthy behaviors into everyday life. Parents were educated on how to use these strategies at home, to further support their children in improving their behaviors. The intervention was developed in cooperation with the participating HLCs and PHCs, intending to comply with the national guidelines and being sustainable in everyday practice. A major strength of this community-based study is the support by the local leadership and collaboration with locally based sports clubs. The main outcomes and corresponding measurements are presented in Table 5. Most instruments are previously validated and have been used in the same age groups as intended in this study.

**Table 5 Tab5:** Description of variables, purpose of measure, what we are to measure, relevant instruments, and when data will be collected

Ecological level	Purpose of measure	Variable	Measure	Instrument	When to collect
Child	SO, IC^a^	Dietary habits	Daily food intake, total energy-intake, meal pattern	FFQ^b^	At inclusion, 6, 12 and 24 months
	SO	Quality of life	Health-related quality of life, well-being	Kidscreen-10	At inclusion, 6, 12 and 24 months
	SO, IC	Motor control	Gross motor coordination	KTK Jumping Lateral^c^	At inclusion, 6, 12 and 24 months
	SO, IC	Physical activity /inactivity	Moderate-to-vigorous intensity physical activity	SenseWear Armband	At inclusion, 6, 12 and 24 months
	SO, IC	Physical activity	Self-efficacy	Described by Motl et al. [60]	At inclusion, 6, 12 and 24 months
	SO, IC	Physical activity	Enjoyment	Described by Motl et al. [60]	At inclusion, 6, 12 and 24 months
	SO, IC	Physical activity	Social support	Described by Sallis et al.	At inclusion, 6, 12 and 24 months
	SO, IC	Sleeping habits	Bedtime resistance, sleep duration, night wakings, daytime sleepiness	CSHQ^d^	At inclusion, 6, 12 and 24 months
	SO	Anthropometric measures	Weight and height (Iso-BMI)	Measured at the Child Health Centers	At inclusion, 6, 12 and 24 months
Parents	SO, IC	Motivation	Form of motivation	TSRQ^e^	At inclusion, 6, 12 and 24 months
	SO, IC	Perceived autonomy support	Support from health care providers	HCCQ 8^f^	6 and 12 months

^a^
*SO* study outcome, *IC* intervention component, ^b^
*FFQ* food frequency questionnaire, ^c^Körperkoordinationstest für Kinder, ^d^Childrens Sleep Habits Questionnaire, ^e^Treatment Self-Regulation Questionnaire, ^f^ Health Care Climate Questionnaire 8

### Step4: Creation of program components and materials

The program components, tools and materials were developed based on the results of the first three steps of the IM protocol and designed to increase healthy lifestyle habits, in particular by encouraging enjoying physical activity and healthy dietary habits, enhancing parental self-efficacy, enhance family engagement and parent-child relationships. The behavioral models and educational strategies include individual parental counselling and follow-up (3-8 meetings) using MI as a counselling method, nutritional courses (4-5 meetings) providing general knowledge and improving practical skills of nutrition for the whole family, and weekly physical activity sessions (1–2 times per week) for children aiming at increasing moderate-to-vigorous intensity physical activity (MVPA) and improving motor control.

Parents will be educated on how to use these strategies at home, to further support their children in improving their behaviors. The intervention material is developed in cooperation with the participating HLCs, intending to comply with the national guidelines and being sustainable in everyday life. Detailed information about program components and materials are presented in Table 4.

### Step5: Planning for adoption and implementation

The purpose of step 5 was to anticipate the adoption and implementation of the intervention study. To do so, representatives from Healthy Life Centre staff, municipality administration, county administration, general practitioners and representatives of three patient organizations were involved at an early stage of the intervention-development process [59]. Prior to conducting the intervention study, representatives of potential implementing organizations and the target group participated in focus-group interviews and in-depths interviews, respectively. This process identified facilitators and barriers for adoption and implementation, described under step 1. By participating in the pilot-study, representatives of the target group, health personnel and those responsible for activity groups helped to modify and improve the program.

#### Design of the study

The present intervention study uses a quasi-experimental controlled design, as the intervention group and the control group are selected without any random pre-selection process. The control group will receive the same intervention as the intervention group with a 6-month delay. The study will investigate whether the intervention has a positive effect both at completion of the 6 months intervention and at long term follow up at 6 and 18 months after intervention period (Fig. 1). During different training sessions, health personnel responsible for recruitment and follow-up of participants have actively participated in developing their role in the implementation process, about the methods and strategies that they would use to facilitate behavioral change and how to use the tools and deliver the materials, which were tailored for the target group. Half-yearly meetings were also arranged where health personnel presented their own experiences and discussed strategies regarding adoption and implementation of the intervention study. In addition, all health personnel involved in the study received a handbook describing how the intervention should be delivered. They also received complete sets of course materials, tailored brochures and information folders etc., for distribution among all study participants (described in Table 4).

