**Methods/design:**

The Intervention Mapping protocol was used to develop a tailored family-based intervention for improving lifestyle habits among overweight and obese children. In order to gather information on local opportunities and barriers, interviews with key stakeholders and a 1-year pilot study was conducted. The main study has used a quasi-experimental controlled design. Locally based Healthy Life Centers and Public Health Clinics are responsible for recruiting families and conducting the intervention. The effect of the study will be measured both at completion of the 6 months intervention study and 6 and 18 months after the intervention period.

An ecological approach was used as a basis for developing the intervention. The behavioral models and educational strategies include individual family counselling meetings, workshops focusing on regulation of family life, nutrition courses, and physical activity groups providing tailored information and practical learning sessions. Parents will be educated on how to use these strategies at home, to further support their children in improving their behaviors.

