### Step6: Development of an evaluation plan

The purpose of step 6 was the development of an evaluation plan. The main objectives specified in step 2 correspond with outcome variables and measurements, of which a detailed overview is described in Table 5. The primary outcome variables, measured at inclusion, at completion of the 6 months intervention and at long term follow up, are children’s MVPA, sedentary time, screen viewing time, eating habits, sleeping patterns and HRQoL as well as parental motivation and support from health care providers. The secondary outcome variables; iso-BMI of the children and parental perception of health will also be measured during pre- and post-testing described in Fig. 1.

In order to conduct a process-evaluation, important enhancers and barriers related to the adoption and implementation were identified by representatives (*n* = 3) involved in the adoption and implementation process in the pilot study. The in depth- interviews of important stakeholders identified the importance and value of having determined and highly committed initiators and project leaders, especially in the process of establishing agreements with the municipality council and other locally based partners. Barriers in the implementation process were related to poor cooperation between the program facilitators, municipal council and the health nurses. Resistance from the participating children’s parents and a lack of program funding were also identified as important barriers of adoption and implementation of the study.

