This intervention study will provide both objectively assessed data and self-reported data on both short-term and long-term effect of a multicomponent approach targeting overweight and obese children and their families. Furthermore, this study will provide practical and accessible tools and materials that can assist health care personnel in their daily practice. This program, if proven effective, may be implemented with contextual adaption in municipal health care institutions in Norway.

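### Controls cross over to the intervention at month 6, so the long-term effect promised for months 12 and 24 has no untreated comparator

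*Protocol article*

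**What the plan says.** In the protocol article, Design of the study, the groups are formed without randomisation ("the intervention group and the control group are selected without any random pre-selection process") and the control condition is a delayed start: "The control group will receive the same intervention as the intervention group with a 6-month delay". The next sentence says the study will look for a "positive effect both at completion of the 6 months intervention and at long term follow up at 6 and 18 months after intervention period".

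The same promise appears elsewhere:
- Abstract, Methods/design: "The effect of the study will be measured both at completion of the 6 months intervention study and 6 and 18 months after the intervention".
- Step 6, evaluation plan: the primary outcomes are "measured at inclusion, at completion of the 6 months intervention and at long term follow up".
- Discussion: the study is to provide data on the "short-term and long-term effect of a multicomponent approach".

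Table 5 sets nearly all measurements "At inclusion, 6, 12 and 24 months", without separating the groups. The test schedule is in Fig. 1, which is not shown in the text available. Population and power calculations gives the only comparison with a stated power. It is between groups, for an MVPA difference of 15 minutes with SD 30, and no time point is named. The text names no other comparator for the period after month 6.

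**The concern.** The programme lasts 6 months and controls start it 6 months late. By the first long-term visit they have had the same treatment, so the study no longer contains anyone who shows what would have happened without it.

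Long-term effect is one of the article's main selling points. Its Background notes that few earlier complex interventions reported long-term results, and its Discussion links wider municipal roll-out to the programme being proven effective. If a month-12 or month-24 group difference were taken as that effect, a lasting benefit could be reported as no benefit, and a fading one as harm. If within-group change were taken as the effect, ordinary change over time in these children could be credited to the programme.

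**Working it through.** **Timeline.** Inputs: 6-month programme and 6-month delay (Design of the study); visits at 0, 6, 12 and 24 months (Table 5). The delay is read as controls starting at about month 6.

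| Month | Intervention group | Control group |
|---|---|---|
| 6 | programme just ended | not yet treated |
| 12 | 6 months after programme | programme just ended |
| 24 | 18 months after programme | 12 months after programme |

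Only the month-6 row sets treated against untreated families.

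**The plan's own figure.** With difference 15, SD 30, two-sided 5% and 80% power, n per group = 2 × (1.960 + 0.842)² × 30² / 15² = 62.8, so 63 by the normal approximation. The t-test version gives 63.8, so 64, with power 80.1% at 64 per group. A one-sided test would need only 50, so the two-sided reading is the one that matches. The stated 64 is therefore right for a 15-minute difference between groups. The design offers a treated-versus-untreated difference of that kind only up to month 6.

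**If months 12 and 24 are compared between groups.** Let r(t) be the share of the effect remaining t months after the programme, with r(0) = 1 and the same 15-minute effect in both groups. The values of r are assumptions; the documents give none.

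Month-12 contrast = 15 × r(6) − 15 × 1. True effect against no intervention in the early group = 15 × r(6). Rejection probability is for a two-sided t-test with SD 30 and 64 per group.

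| r(6) | True effect (min) | Expected contrast (min) | Rejection probability |
|---|---|---|---|
| 100% | +15 | 0 | 5.0% |
| 75% | +11.25 | −3.75 | 10.8% |
| 50% | +7.5 | −7.5 | 28.9% |
| 25% | +3.75 | −11.25 | 55.8% |
| 0% | 0 | −15 | 80.1% |

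Month-24 contrast = 15 × r(18) − 15 × r(12). With a constant retention q per 6 months, this is 15 × (q³ − q²).

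| q | True effect, early group (min) | Expected contrast (min) | Rejection probability |
|---|---|---|---|
| 100% | +15 | 0 | 5.0% |
| 90% | +10.9 | −1.2 | 5.6% |
| 75% | +6.3 | −2.1 | 6.8% |
| 50% | +1.9 | −1.9 | 6.4% |
| 25% | +0.2 | −0.7 | 5.2% |

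At month 24 the test hardly rejects more often than its nominal level, whether the true effect is 15 minutes or almost nothing. An effect that levels off by 12 months after the programme also gives 0. Only a marked loss between 12 and 18 months after the programme would give a larger negative contrast. A positive contrast at either visit would need the effect to grow after the programme ends, and even then it would not measure the effect against no intervention.

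**If months 12 and 24 are assessed within groups.** The change from the pre-intervention value contains the effect together with the age trend over one to two years in children aged 6–10. It also contains regression to the mean in children selected for iso-BMI ≥ 25, which bears most directly on iso-BMI. Season enters wherever the two visits fall half a year apart, as with a month-6 starting value and a month-12 follow-up. No concurrent untreated group is available to separate these from the effect.

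**The case against.** The strongest reply is that the document never says the groups will be compared at months 12 or 24. The power statement names no time point and fits month 6, which the crossover leaves intact. Timing the follow-up from the end of the intervention is compatible with following treated families within group. That stands. A reader might infer that the study will report a long-term effect of the wrong size or sign, but this would follow only if a later between-group difference were tested and read as the effect. The text does not commit to that.

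A reader might also infer from Table 5 that controls are never measured 6 or 18 months after their own programme. The documents do not support this either. Table 5 does not list times by group, and Fig. 1, which is not shown, could give controls a shifted schedule or extra visits.

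Nor should the month-12 sign reversal be carried over to month 24. There the contrast is close to zero under steady fading, so the problem is lack of information rather than a sizeable reversal.

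It can also be said that delayed-start controls are common, that the delay is openly stated, and that an article leaves analysis detail to a plan not shown. All true, and offering controls the programme is not the issue. But the crossover and the long-term promise stand side by side in this document, and no figure or analysis plan can bring back an untreated group after month 6.

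**Conclusion.** The concern holds in limited form. The effect against no intervention can be estimated with a concurrent control only up to month 6, and even then between non-randomised groups. At months 12 and 24 the study offers either a comparison of early with delayed treatment or an uncontrolled within-group change. Neither is the long-term effect that the Abstract, Design of the study and Discussion promise.

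The size of the possible error depends on a between-group reading, on an equal 15-minute effect in both groups and on assumed retention. Under these, the month-12 contrast falls short of the true effect by 15 minutes at every retention level, because the controls' own fresh effect is subtracted. The month-24 contrast is about 0 to −2 minutes under constant fading, whatever the true effect. The month-6 comparison and its sample-size basis of 64 per group are not affected by this point.

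**What to change.** 1. Limit the controlled effect claim, in the aims and in any analysis plan, to the between-group comparison at month 6.
2. Describe months 12 and 24 as uncontrolled maintenance in treated families, by time since each family's own intervention start. For controls, use the month-6 value as the pre-intervention value where the test schedule in Fig. 1 allows.
3. State that no between-group difference at month 12 or 24 will be read as the effect against no intervention.
4. Align the Abstract, Design of the study and Discussion with this wording.

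The cost is some rewording and one analysis rule, with no new visits and no change to what families are offered. What is lost is a controlled long-term claim that the design does not support. How far the two groups can be lined up by time since start depends on Fig. 1, so the maintenance results should be presented as descriptive.
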